### Data storage and statistical analysis of the trial outcomes

The data compilation form containing the variables of interest will be completed by the corresponding researcher at each center. Data will be documented in the paper CRF by researchers or evaluators and will be double-checked by quality inspectors. The supervisor will inspect the progress of the trial at regular intervals in each branch center. All the detailed original data (paper CRF) will be recorded timely, clearly, and completely. The case reports will be modified only by researchers who are documenting the data. The correct method of modification is tomark a line through the original record and write the revised data next to the original data,so that the change may be clearly visible. The modified data will be documented with data and the initials of the investigator. All the materials will be kept for 5 years after the completion of the study. At each center, the information obtained will be recorded on an electric database by EpiData software 3.1 at the same time, for subsequent statistical analysis.

Predictive Analytics Software (PASW, version18.0) is used for data analyses. Exploratory analysis will include the minimum, maximum, median, mean, and standard deviation. For measurement data, a normality test is necessary. Furthermore, baseline categorical data, demographic characteristics, such as sex and age category, and numerical data are analyzed with chi-squaretests and one-way analyses of variance (ANOVA). Student’s *t*tests are used tocompare different periods of measurement data. Wilcoxon matched-pairs signed-rank tests are used for ranked data. Independent Student’s *t*tests and 95% confidence intervals are used to detect differences between groups of the measurement data only if the normality test and analysis of variancetestsprove significant, otherwise rank-sum tests should be used, which are also used to detect differences between groups of ranked data. Linear mixed models (for continuous outcome variables) and generalized estimating equations (for categorical outcome variables) are used to examine changes over time and the severity of PSQI and HAMD. Both intention-to-treat and per-protocol analyses are used. Data from participants who do not violate the treatment protocols will be included in the per-protocol analysis. Missing data are dealt with using the ‘last value carried forward’ method.

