### Design

This is a multicenter, randomized, controlled prospective study. Participants receive optimized acupuncture (treatment group), or conventional acupuncture (control group) in a 1:1 allocation ratio (Figure 1).

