#### Sample size calculation

The sample size calculation is based on the two-sided chi-square test for difference with respect to the primary endpoint. There are few reports in the literature of clinical trialsof acupuncture treatment for depression insomnia. Based on our earlier randomized controlled pre-trial in Guangdong Provincial Hospital of TCM, we decided to adapt the reduction of the HAMD and PSQI scores as a baseline for the sample size calculation for our trial. We believe that the successful cure rate for depression insomnia is approximately 40% when adopting the conventional acupuncture formula and should be increased to 70% or more when using the optimized acupuncture formula. A sample size of 58 patients per group is necessary (as calculated using PEMS version3.1 software,with the predicted cure rates of 40% and 70%). The maximum dropout rate within the intervention is expected to be about 15%. Therefore, another 24 patients in total have to be randomized to obtain the required number of patients. The total number of patients needed to be randomized is therefore 140.

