#### Primary outcomes

The PSQI, to ratesleep disorders, and HAMD, to rate depression, were applied as primary outcome measurements for effectiveness evaluation. The construction validity and reliability of the PSQI to measure changes in sleep qualityhave been proven in previous studies and this scale has been validated for use in China. The PSQI comprises 19 self-rated questions and 5 otherquestions, all grouped into seven component scores (subjective sleep quality, sleep latency, sleep duration, sleep efficiency, sleep disturbance, hypnotic medication use, daytime dysfunction), each weighted equally on a four-point scale, from 0 to 3. The seven component scores are then added to provide aPSQI score. A cutoff score of 5 has been recommended, with scores >5 indicating subjective insomnia [18]. Changes in levels of depression were measured on the Hamilton hetero-evaluation scale. There are three types of HAMD scale, with 17, 21, and 24 items. We used the 24-item HAMD scale. This scale is of proven discriminant validity, reliability, and sensitivity to change; moreover, it has been validated for use in China. According to the scoring standard, a normal score is less than 8; a score ≥8 and <20 indicates thatthe patient may have depression; a score of ≥20 and ≤35 indicates thatthe patient definitely has depression; anda scorehigher than 35 indicates that the patient has severe depression. In general, the higher the score, the more severe the depression [19].

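### The rule choosing between the t test and the rank-sum test is reversed as printed, and its ANOVA condition makes the confidence interval depend on the result

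*Protocol article*

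**What the plan says.** All but the last three items are in the protocol article under Data storage and statistical analysis of the trial outcomes.

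- A preliminary check is required: "For measurement data, a normality test is necessary". Neither the test nor its level is named.
- Independent t tests and "95% confidence intervals are used to detect differences between groups of the measurement data", but "only if the normality test and analysis of variancetestsprove significant, otherwise rank-sum tests should be used".
- The section uses the term analysis of variance for a comparison of means at baseline: "one-way analyses of variance (ANOVA").
- The next sentence adds "Linear mixed models (for continuous outcome variables) and generalized estimating equations (for categorical outcome variables"), to look at change over time and severity of PSQI and HAMD.
- Under Primary outcomes, the PSQI and HAMD scales "were applied as primary outcome measurements for effectiveness evaluation".
- Under Design there are two arms "in a 1:1 allocation ratio".
- Under Sample size calculation the basis is a "two-sided chi-square test for difference with respect to the primary endpoint".

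The article does not say which of these analyses is the main between-arm comparison.

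**The concern.** The rule has two conditions, and both are faulty.

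**Direction.** A normality test has normality as its null hypothesis. A significant result therefore speaks against the t test's assumption, yet here it is the ticket to the t test. Data that show no departure from normality go to the rank-sum test.

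**Second condition.** Read as one-way ANOVA, it asks whether the means differ before allowing the test of whether the means differ. Read as a test of equal variances, it is reversed in the same way as the first condition.

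The interval is attached to the t-test branch only. At stake is whether readers get an estimated arm difference in PSQI and HAMD with its uncertainty, and whether that depends on the result.

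**Working it through.** **Inputs.** From the article: two arms, 1:1; 58 per group needed; 140 randomized, so 140/2 = 70 per arm. Assumed, because the article does not give them: Shapiro-Wilk in each arm (significant if either arm is), every test at 5%, and the score distributions below.

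**The plan's own figure.** This point disputes no number; 58 serves only as the simulated size. With cure rates of 40% and 70%, two-sided 5%, 90% power (alpha and power assumed) and mean rate 0.55: n = [1.960·√(2·0.55·0.45) + 1.282·√(0.40·0.60 + 0.70·0.30)]² / 0.30² = (1.379 + 0.860)² / 0.09 ≈ 55.7, so 56 per arm, close to 58.

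**Circularity.** With two groups, the between-group mean square is (n₁n₂/(n₁+n₂))·(ȳ₁−ȳ₂)² on 1 degree of freedom, and the within-group mean square is the pooled variance s². Hence F = (ȳ₁−ȳ₂)² / [s²(1/n₁+1/n₂)] = t². On the ANOVA reading, any interval that is reported excludes zero. At 58 per arm the critical t on 114 degrees of freedom is 1.981, so the observed difference must exceed 1.981·√(2/58) ≈ 0.37 pooled SD. At 70 per arm it is 1.977·√(2/70) ≈ 0.33 SD.

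**Simulation of the literal rule.** 5,000 trials per setting. PSQI-like means rounded scores limited to 0–21, mean 10, SD 4. Skewed means gamma with shape 2. Each cell shows 58 / 70 per arm.

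| Scores | True difference | No interval, ANOVA reading | No interval, equal-variance reading (Levene) |
|---|---|---|---|
| Normal | 0 | 99.4% / 99.6% | 99.3% / 99.4% |
| Normal | 0.5 SD | 92.4% / 91.7% | 99.5% / 99.5% |
| PSQI-like | 0 | 99.3% / 99.4% | 99.3% / 99.0% |
| PSQI-like | 0.5 SD | 87.4% / 84.4% | 98.9% / 98.6% |
| Skewed | 0 | 95.4% / 95.5% | 95.4% / 95.4% |
| Skewed | 0.5 SD | 23.2% / 16.7% | 95.2% / 95.2% |

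**Rejection rates, ANOVA reading, 58 per arm.**

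| Scores | True difference | Literal rule | t test alone | Rank-sum alone |
|---|---|---|---|---|
| Normal | 0 | 4.5% | 4.7% | 4.3% |
| PSQI-like | 0 | 5.4% | 5.3% | 5.2% |
| Skewed | 0 | 6.1% | 4.6% | 4.5% |
| Normal | 0.5 SD | 74.8% | 76.3% | 74.4% |
| PSQI-like | 0.5 SD | 74.9% | 76.2% | 74.2% |
| Skewed | 0.5 SD | 89.3% | 76.9% | 88.8% |

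At 70 per arm, power with normal scores is 82.4% against 83.8%. A separate 4,000-trial run at 58 per arm gave 73% against 76%, and type I error of 7.6% for lognormal (sigma 0.8) and 6.8% for exponential scores.

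**Type I error under both readings.** A further run of 20,000 null trials at 58 per arm gave:

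| Scores | ANOVA reading | Equal-variance reading | Either test alone |
|---|---|---|---|
| Normal | 5.0% | 4.9% | 4.9–5.0% |
| PSQI-like | 5.4% | 5.2% | 5.2% |
| Gamma, shape 2 | 6.8% | 6.1% | 5.1% |
| Exponential | 7.1% | 6.5% | 4.8–5.0% |
| Lognormal, sigma 0.8 | 7.6% | 6.9% | 5.0–5.1% |

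The rise comes with skew and is smaller on the equal-variance reading.

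**Conventional direction** (t test and interval when normality and equal variance are not rejected): the interval appears in about 86–87% of trials with normal scores, 78–83% with PSQI-like scores and about 0% with clearly skewed scores.

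**The case against.** The best defence is that this is a language slip. Normality and equal variances are the usual conditions for a t test, so the authors may have meant that both are satisfied. The article refers to a pre-specified analysis plan that is not shown, and an analyst would probably apply the usual direction. This lowers the expected harm, but the published rule still instructs the opposite, and the section's own use of the ANOVA term does not support the charitable reading.

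A reader might infer four stronger things. The documents do not support them.

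- **That this is the only between-arm analysis of PSQI and HAMD.** The next sentence assigns linear mixed models to those scores, and in a two-arm trial such a model could give an arm difference with an interval. The text does not make it the between-arm comparison, so it does not repair the rule either.
- **That the trial would use an invalid test.** The rank-sum test is valid on normal data and costs little power.
- **That type I error is inflated in general.** With normal or PSQI-like scores it stays near 5%. The rise needs clear skew, and the article gives no score distribution. PSQI is a bounded sum of seven components scored 0 to 3, so an unbounded lognormal is an unfavourable case.
- **That an interval is nearly always missing.** With skewed scores and a real 0.5 SD difference, the ANOVA reading yields one in 77–83% of trials, though only because the result is already significant.

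**Conclusion.** The point holds, and it should be fixed. The reversal of the normality condition follows from the text alone, however the second condition is read. The circularity holds if analysis of variance means one-way ANOVA; if equal variances were meant, it disappears and the second condition is reversed instead.

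The damage is mainly to estimation and reporting. With roughly normal scores the literal rule withholds the interval in about 84% to over 99% of trials, and on the ANOVA reading it reports one only when zero is excluded. The effect on error rates is secondary: about 1.5 to 3 points of power with normal scores, and type I error of about 6 to 7.6% with clearly skewed scores on the ANOVA reading.

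The percentages rest on the assumed distributions, Shapiro-Wilk and 5% levels. The reversal and the F = t² identity do not.

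**What to change.** Delete the rule that makes the test depend on preliminary significance. Name one between-arm analysis of PSQI and HAMD; the linear mixed model already in the section is a natural candidate. Report the end-of-treatment arm difference with its 95% confidence interval whatever the preliminary tests show. Keep the rank-sum test as a sensitivity analysis, run regardless of the normality result. The choice of model terms can stay with the analysis plan.

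At the least, correct the direction of the rule, replace the ANOVA condition with an equal-variance condition, and report the interval unconditionally. Correcting the direction alone is not enough, because with clearly skewed scores the interval would then almost never appear.

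The cost is wording. No new data are needed and the sample size does not change. The article says that the trial concluded in 2011, so the correction bears on how the results are analysed and reported. If the unseen analysis plan already states a sound rule, the article should be brought into line with it.

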### Study organization

Statistical analysis will be carried out by the Design,Measurement and Evaluation in Clinical Research (DME) professionalsin Guangzhou University of TCM, after approval of the protocol by the Ethics Committee of Guangzhou Provincial Hospital of TCM, 2008GL-26, 2009-07-01. The trial is internationally registered at Chinese Clinical Trial Register http://www.chictr.org/ (ChiCTR-TRC-00000481). A training working team will be established, consisting of DME professionals of Guangzhou University of TCM, staff of the scientific research department and staff of the General Acupuncture Department. The principle institution is Guangdong Provincial Hospital of TCM and the cooperative institutions are the Second People’s Hospital of Zhao Qing city and the People’s Hospital of Hui Zhou. Data management and statistical analysis will be carried out under the guidance of DME professionals according to a pre-specified statistical analysis plan. The clinical trial quality control group will be established, and the investigator in each branch center will be responsible for quality control.

## Discussion

Depression has various clinical manifestations and insomnia is one of the most frequently occurring symptoms. Clinically, we are not simply using regulating spirit and regulating liver acupuncture formula. The formula has been optimized. Lie Que (Lu-7) and Zhao Hai(Kid-6) are two of the confluent points. The actions of these two points can be best understood in relation to the regulation of various meridians, three Jiao, and relative organs. These two empirical points are used as the main points and embedded needles are buried to consolidate the curative effects of the acupuncture.

## Trial status

The project was concluded in the 2011 and we expect to publish the result at the end of 2013.

## Abbreviations

ANOVA: Analysis of variance; CRF: Case report file; DME: Design, measurement and evaluation in clinical research; HAMD: Hamilton rating scale for depression; NSAID: Nonsteroidal anti-inflammatory drug; PASW: Predictive analysis software; PSQI: Pittsburgh sleep quality index; SRICTA: Standards for reporting interventions in clinical trials of acupuncture; TCM: Traditional Chinese medicine.
